**Figure 1 F1:**
[figure not shown]
GANTT presentation of the project timeline.

**Inclusion criterion:** All young people arriving at the juvenile institutions will be offered to participate in the study.**Exclusion criteria:** Serious physical illness prohibiting participation in physical activities. Inability to read and understand at least one of the following languages: Swedish, Arabic, or Dari (variety of Persian spoken in Afghanistan).**Inclusion criterion for the qualitative data collection:** Participation in the yoga intervention.**Exclusion criteria for the qualitative data collection:** Inability to understand and speak Swedish language.

### Procedure

Upon placement to the juvenile institution, the young people will be offered to participate in the study. Participation is voluntary, and SiS clients are ensured that participation in yoga or in a comparison group or non-participation should not affect the care they receive at SiS. All data is coded (pseudo-anonymized) and the code keys will be kept securely at each juvenile institution under the institution directors' responsibility, following SiS regulations. Upon completion of data assessment code keys will be destroyed. Only anonym data will be handled outside each SiS facility. With this procedure we assure that there is no possibility of identifying the individual from the collected information.

The study has a *quasi-experimental* design. Participants will receive a numeric code and will participate in the pre-intervention assessment, after which they will chose to participate in yoga classes (belonging to the “yoga group”) or not to participate in yoga classes (belonging to the “comparison group”) (Figure 2). The yoga group will participate in a 75 min yoga session, twice a week, for six weeks—as their leisure-time physical activity. During the same six-week period, the comparison group will participate twice a week (~1 h) in any, at the institution offered leisure-time physical activity (e.g., walking, gym training, and physical education class). Participants of the comparison group are asked to include ~10–15 min of relaxation at the end of their leisure-time physical activity.

**Figure 2 F2:**
[figure not shown]
Flowchart of the quasi-experimental study design, and list of the included measures at pre- and post-intervention.

#### Ethnicity

An essential aspect of our study is the inclusion of all major ethnic groups who are SiS clients. We have investigated how many languages spoken by most of the young people placed in SiS institutional care. As a result, we will offer the various test materials in Swedish, Arabic, and Dari, thus ensuring that almost 100% of the presumptive participants can take part in the study, independently of their ethnic belonging.

### Yoga Classes

The yoga classes held twice a week consist of trauma-informed yoga methods including inviting language, freedom of choice by offering options, a set routine for predictability and recognition, counting down in challenging poses for a sense of control and guidance toward practical interoceptive awareness. The relaxation offered is a progressive muscle relaxation adapted for ADHD and high anxiety levels. The aim is to increase resilience, promote relaxation and to provide self-regulation skills for stress and overwhelming emotions and reactions promoting self-empowerment and impulse control. The class will be set up in a circle to provide a sense of safety with no outer disturbances for triggering responses and will always be offered on a voluntary basis for the participants.

A yoga class is 75 min long and consists of yoga methods such as physical movement, static yoga postures, balance exercises, and breathing practices. The instruction intends to increase the interoceptive awareness with practically adapted mindfulness and guided trauma-informed progressive relaxation. The class includes intervals of raising and lowering heart rate and breathing to provide self-regulating skills. The classes do not consist of potential triggering poses, no physical adjustments or practices that can bear a resemblance to sexual abuse or practices that can over-activate the sympathetic nervous system.

Each class is built up as follows:

Warm-up 15 min: At least 10 min of warm-up exercises to release muscular tension, discharge high-stress levels, restlessness, and anxiety, increase blood circulation, and increase proprioceptive awareness.Opening sequence 15 min: large energizing dynamic movements.Balancing poses 10 min.Dynamic Sequence 15 min: a combination between dynamic energizing movements and powerful postures where the participants hold the pose for at least two min (impulse-control). The importance of synchronized breathing and movements.Closing 20 min: including the last 10 min with guided mindfulness-based relaxation.

The instructors have completed a special training program in trauma-informed yoga and yoga for mental health, and they are trained in how to manage overwhelming emotions in a class. The classes are adapted to the most common mental health issues presented within the juvenile institutional system, such as PTSD, anxiety disorders, depression, ADHD, and autism.

The yoga manual is standardized, and all yoga instructors are qualified by a specific yoga-informed education course, held by licensed yoga therapist [name] (e-RYT 500, YACEP, and TCTSY-F), founder of Trauma-adapted (informed) Yoga Sweden. She is the main teacher and Program director for the Prison Yoga Project Europe, recognized as a part of Trauma Research Foundation Therapeutic Alliance.

### Assessment

There will be two main testing periods: pre-intervention (Test 1) before the intervention and post-intervention (Test 2) after six weeks of intervention (Figure 2). All the measures described below will be included in the pre- and post-intervention tests.

### Measures

Three different origins of data are included as measurements: (A) self-reported measures in the form of a survey, (B) heart rate measure, and (C) register data. A and B applied both at pre-intervention (Test 1) and post-intervention (Test 2), while the data from SiS's register will be combined with data only for those participants who complete all parts of the study.

The pre-intervention survey includes a question on yoga expectations, and the post-intervention assessment includes a question on time spent on yoga and the experience of yoga.

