##### Brief Symptom Inventory

The Brief Symptom Inventory (BSI) is a self-rated measure of general psychopathology and psychological distress (39). The BSI contains 53 items reflecting psychological symptom patterns of psychiatric patients and non-patients. It comprises nine primary symptoms' scales and the global severity index (GSI). The primary symptom scales are: Anxiety, Depression, Interpersonal Sensitivity, Hostility, Obsessive Compulsiveness, Psychoticism, Paranoid Ideations, Phobic Anxiety, and Somatization. The answers are given on a five-point scale, from 0 = “not at all” to 4 = “extremely.” The BSI subscales and its GSI have high internal reliability (0.71–0.85) (9, 40, 41) and test-retest reliability, as well as high convergent, discriminant, and construct validity (42).

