### Data Analysis

If the required number of male and female participants (at least 34 of each gender) is reached, then we will analyze the data separately by gender. Otherwise, the data will be pooled, and no gender-specific results will be presented.

All statistical analyses will be conducted using a significance level of *p* <0.05. Only complete post-attrition data will be analyzed. The comparison of the attrition rates between the two groups (“yoga” group and “comparison” group) will be calculated using Fisher's exact test. The Test 1 and 2 scores within the groups will be compared using the Wilcoxon signed-rank test. Mean changes and standard deviations will be calculated to identify differences within the groups. Mann–Whitney *U-*tests will be used for the continuous variables and Fisher's exact test for the categorical variables to compare differences between them. The effect sizes (Cohen's *d*) will be calculated to identify differences between the groups; an effect size of 0.2 will be considered a small effect, 0.5 a medium effect, and 0.8 a large effect. As data will be collected from three institutions, generalized estimating equations (GEE), that adjusts standard regression estimators for clustering, will be applied. The primary outcome is the level of psychological distress (BSI). Secondary outcomes' (craving, pain, affect, and aggressive antisocial behaviors) mediating and moderating effect will be also explored by conditional process analyses. We plan to conduct a mid-point analysis (about nine months after that data collection has started) to allow for better modeling of change trajectories.

To describe the adolescents' experiences of participating in yoga practice, with the help of a semi-structured interview guide (Supplementary Material), individual interviews will be performed. The adolescents will be contacted within 2 weeks after completing the yoga intervention. Content analysis will be used as a method for analyzing the interviews (52). The qualitative content analysis is performed stepwise identifying meaning units, condensing the meaning units, labeling meaning units with codes and thereafter identifying subcategories, categories ant themes. Content analysis makes it possible to describe the adolescents' experiences on both manifest and latent levels.

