The duration and the type of yoga in the present study have been adjusted to the population. We use a shorter intervention time but more frequent training (six weeks twice a week, implying 12 yoga sessions) to optimally adapt to the participating institutes' possibilities. Several studies have proven that 8–10 weeks (once a week, therefore, 8–10 sessions) yoga has positive effects on mental health, behaviors, and self-control of adults in correctional setting (9, 25–27, 53). As our study population includes adolescent, it is essential to recognize that the brain goes through pruning (anatomically improving its efficiency) during this developmental period [see e.g., (54)]. During this time, the brain is increasingly susceptible to environmental effects; therefore, we speculate that eventual changes in adolescents' mental health and behaviors will be recognizable already after six weeks (12 sessions) of training. There are results indicating that short-term intensive interventions (four weeks, three times a week yoga classes) have a positive effect on adults' anxiety, depression, and stress (55). Importantly we use a specifically developed yoga (trauma-informed yoga), adapted to the most common psychiatric disorders (ADHD, PTSD, anxiety, and depression) in the adolescent study population.

The proposed study fills a gap in knowledge focusing on young people population in institutional care. If the study's hypothesis is confirmed, our results will verify and strengthen earlier findings in Sweden (9, 25, 26) regarding the benefits of yoga for a marginalized population, thus indicating the usefulness and value of yoga within juvenile institutional care at a national level.

One limitation of the proposed study is the fact that we won't be able to randomly distribute participants between groups, with other words, we could not rationalize a randomized controlled trial (RCT) design. A quasi-experimental design was chosen in agreement with the clinical and institutional experts, who predicted an unacceptable high attrition rate (80–90%) in case of not giving the possibility to the young clients to freely choose their participation in yoga classes.

Future RCTs should confirm our findings and prospective longitudinal studies need to investigate if yoga within SiS can potentially offer a prosocial activity upon release from institutions for young people.

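### Yoga expectation is asked before adolescents choose their group but has no stated role in the analysis, so an expectation difference between the self-chosen groups could pass as a yoga effect on self-rated distress

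*Protocol article*

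**What the plan says.** Under Procedure, participants "will participate in the pre-intervention assessment, after which they will chose to participate in yoga classes" or to be in the comparison group. The Discussion gives the allocation as a limitation: "we won't be able to randomly distribute participants between groups". Under Measures, "The pre-intervention survey includes a question on yoga expectations"; nothing is said about its wording or response format.

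The Data Analysis section names the BSI as primary outcome, and the instrument's own section says: "The Brief Symptom Inventory (BSI) is a self-rated measure of general psychopathology and psychological distress". The secondary outcomes listed there (craving, pain, affect, aggressive antisocial behaviour) also come from the self-report survey.

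For the comparison of groups, Mann–Whitney U "tests will be used for the continuous variables and Fisher's exact test for the categorical variables to compare differences between them". Wilcoxon signed-rank tests are used within groups. GEE is to be applied because data come from three institutions, and conditional process analyses will explore the listed secondary outcomes as mediators and moderators. Expectation is not mentioned in that section, and no baseline covariate is named.

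**The concern.** Adolescents who think yoga will help them may be more likely to choose it, and more likely to report feeling better afterwards. If both hold, the yoga group's reported improvement contains a part that would be there even if yoga did nothing.

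This differs from imbalance in baseline severity. Two groups with the same Test 1 BSI can still separate at Test 2 if one of them expects benefit and reports accordingly, so adjusting for Test 1 BSI alone does not deal with it.

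The plan collects a variable that bears directly on this rival explanation, at the right time, and then fixes a between-group test that cannot use it. The Discussion says that a positive result would support investment at national level, so the explanation deserves a planned check.

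**Working it through.** **The plan's own figure.** The sample size of 34 per sex reproduces. For the within-between interaction, λ = N·f²·m/(1 − ρ), with f = 0.25, m = 2 and ρ = 0.5 (ρ is not stated; assumed). This gives λ = 34 × 0.0625 × 2 / 0.5 = 8.5 on 1 and 32 df, and power 0.807. The figure does not bear on the present point except for scale. With 17 per group, λ = d²·17/2, so λ = 8.5 means a planned difference of d = 1.0 SD of change.

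**Inputs from the protocol.** About 120 recruited and attrition up to 50% leave 60 completers, or 30 v 30 if split equally (split assumed). A single-sex analysis at the minimum of 34 is 17 v 17 (split assumed).

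**Inputs assumed, because the documents give none.** The expectation gap between choosers and non-choosers is 0.5 to 1.2 SD. The correlation of expectation with self-reported change is r = 0.2 to 0.3, with the same slope in both groups. Yoga has no true effect.

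**Spurious difference.** d = gap × r. Two-sided 5% rejection rates come from the noncentral t distribution:

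| Gap (SD) | r | Spurious d | 30 v 30 | 17 v 17 |
|---|---|---|---|---|
| 0.5 | 0.2 | 0.10 | 6.7% | 5.9% |
| 0.8 | 0.2 | 0.16 | 9.4% | 7.4% |
| 0.8 | 0.3 | 0.24 | 15.0% | 10.4% |
| 1.2 | 0.3 | 0.36 | 27.8% | 17.5% |

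A simulation with the Mann–Whitney test itself (3,000 runs per setting, 30 v 30) agrees: 5.7% at gap 0.5 and r = 0.2, 9.7% at 0.8 and 0.2, and 13.8% at 0.8 and 0.3. With expectation as a linear covariate, the spurious difference is close to zero and rejection is 4.1% to 5.5% throughout. That clean result depends on the equal-slope assumption.

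**If expectation acts only in those doing yoga.** Let the slope be b in the yoga group and 0 in the comparison group, with equal group sizes and equal expectation variances. Let mY (positive) and mC be the group means, measured from zero expectation.

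- Raw spurious difference: b·mY.
- Pooled additive slope: b/2.
- Adjusted difference: b·mY − (b/2)(mY − mC) = b(mY + mC)/2.
- Share remaining: 1/2 + mC/(2mY).

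At least half remains whenever mC ≥ 0. For example, mC = 0.5 and mY = 1.3 leave 0.5 + 0.5/2.6 = 69%. An additive covariate alone is therefore not enough.

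**Precision cost of the additive model.** The standard error grows by √(1 + (gap/2)²), before any gain from reduced residual variance. This is √1.16 = 1.08 at a gap of 0.8 and √1.36 = 1.17 at a gap of 1.2.

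**The case against.** The strongest reply is that silence is not a decision. GEE is a regression method and can carry covariates; the article does not call it unadjusted, and covariate lists are often left to an analysis plan that is not shown. A reader might infer that the study has decided never to use expectation, and the document does not support that. What stands is narrower: the article fixes the between-group tests as ones that take no covariates, gives GEE one purpose (clustering), and names the variables for the process analyses without expectation. Followed as written, the plan leaves the item unused. The planned Mann–Whitney and Fisher comparisons might extend to describing expectation by group, but the text does not say so.

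A reader might also infer that yoga choosers do expect more and that the result will be biased. Nothing in the document shows this; it is plausible and unmeasured. With a modest gap the false-positive rate is almost nominal.

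Three further points stand. HRV and register data are not self-reports, so the reporting-bias argument concerns the survey outcomes, although these include the primary one. The comparison group is also active, at the same frequency and with a short relaxation period, which may offset part of any non-specific effect. The item's format is unknown and may not yield a usable score.

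Finally, adjustment can give false assurance. By the algebra above, an artefact confined to the yoga group could keep most of its size after additive adjustment. That rules out treating a surviving estimate as proof of an effect beyond expectation.

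**Conclusion.** The point holds in a limited form. A pre-choice variable that may be related both to the choice of group and to self-reported change is collected but given no stated role. Under the plan as written, any part of the group difference due to expectation would be attributed to yoga.

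The size is not known. Over the assumed range the artefact is d = 0.10 to 0.36, roughly a tenth to a third of the planned difference of 1.0 SD of change (at ρ = 0.5). The false-positive rate is about 6 to 7% at the low end and about 28% at the high end with 30 v 30 completers, and about 6% to 18% with 17 v 17. These figures rest on assumed gaps, correlations, equal splits and a common slope.

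The document does not support saying that the bias is present, that it is large, or that adjusting for one item would remove it. The broader problem of self-selection, which the Discussion concedes, would remain. The change is still worth making because the item is already in the survey and the analysis is cheap.

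**What to change.** In the Data Analysis section:

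1. Report the expectation item by group, and state its wording and response format.
2. Pre-specify that the planned GEE for Test 2 BSI includes Test 1 BSI as a covariate.
3. Add a pre-specified sensitivity version of that model with the pre-choice expectation item and its interaction with group. Give the yoga-minus-comparison difference at stated levels of expectation, because with an interaction the group coefficient alone depends on how expectation is centred.
4. Describe this as a sensitivity analysis that reduces but does not remove self-selection and expectation bias. Do not attach a rule under which surviving adjustment entitles the study to claim an effect beyond expectation.

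No new data, participants or procedures are needed, provided the item can be scored; if it is free text, only step 1 and the Test 1 adjustment are straightforward. The cost is one extra model and a somewhat wider interval: a standard error about 8 to 17% larger for the additive term at gaps of 0.8 to 1.2 SD, and more with the interaction. It should be fixed before outcome data are examined, including at the planned mid-point analysis.

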#### A. Self-Reports

The self-report survey will include six previously validated instruments available in the Swedish, Arabic, and Dari languages.

##### Juvenile Care Adjusted Measure of Aggression

It is a SiS environment adapted version of the Prison Adjusted Measure of Aggression (PAMA), which assesses the self-reported frequency of state aggression and antisocial behavior in subjects within correctional settings (37). The Juvenile Care Adjusted Measure of Aggression (JCAMA) scale consists of nine items. The items are distributed over three subscales: a five-item Aggression scale, a two-item Antisocial Behavior scale, and a two-item Self-directed Aggression scale.

The Aggression subscale measures overt aggression and includes items on temper tantrums, verbal and indirect aggression, non-specific fighting, and physical assault against people. The Antisocial Behavior subscale consists of items on disciplinary problems at school and conflicts caused by own antisocial behavior. The Self-directed Aggression subscale includes items on self-injurious behavior and suicide attempts.

All the items are rated on a six-point scale based on the total number of occurrences over the past month: no occurrences = 0, one event = 1, two or three events = 2, four to nine events = 3, 10 or more events = 4, more events than can be counted = 5. The JCAMA score is the sum of the ratings on all nine items (total score) or the specific items in a certain subscale (subscale score). The JCAMA total score can range from 0 to 45; the Aggression subscale scores from 0 to 25; the Antisocial behavior scores from 0 to 10; and the Self-directed Aggression scores from 0 to 10.

The original PAMA's validity has previously been shown to be acceptable, and its test-retest reliability has been measured as fair (37), while the JCAMA reliability has not yet been tested.

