## Methods

### Participants

Computer required sample size analysis for repeated measures ANOVA within-between interaction, with an effect size of 0.25 [medium effect size; average from effect sizes in changes by yoga in previous studies (9, 25)], a power of 0.80, an alpha error probability at 5%, for two groups (yoga and comparison) and two measurements (pre-and post-intervention) suggested a sample size of 34 for each sex.

We aim to collect complete data from at least 34 participants of both sexes (34 male and 34 female clients) to perform gender-specific analyses. Gender analyses will only be performed, if this number of participants can be reached.

Based on previous experience working with participants within correctional settings, we know that the attrition rate can reach 50%; therefore, our aim is to include approximately 120 participants.

Three institutions at the South West in Sweden have at this stage declared interest in participating in the study. Data collection is planned to take place for one and a half years' time, based on an estimated three months per institute (Figure 1). This three months period includes spreading advertisements and information about the study, collecting informed consents, six weeks of intervention (including pre- and post-intervention tests), and time for qualitative interviews to assess individual experiences of yoga classes. As the average time spent within SiS is calculated to be eight months, we will be able to perform intervention and data collection in each participating institute twice, six months apart during the planned data collection period (one and a half years) (Figure 1).

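### The time from placement to Test 1 is not fixed, so for recent arrivals the one-month JCAMA baseline mixes pre-placement and institutional behaviour, while Test 2 covers institutional time only.

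*Protocol article*

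**What the plan says.** Four parts of the Methods bear on this point.

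- **Enrolment.** The inclusion criterion after Figure 1 reads "All young people arriving at the juvenile institutions will be offered to participate in the study". The Procedure section agrees: "Upon placement to the juvenile institution, the young people will be offered to participate in the study". The pre-intervention assessment follows, and adolescents then choose yoga or the comparison activity.
- **Test dates.** The Assessment section has two tests: "pre-intervention (Test 1) before the intervention and post-intervention (Test 2) after six weeks of intervention". Neither date is tied to the date of placement, and no minimum stay is required.
- **Waves.** The Participants section allots three months to each institution: "This three months period includes spreading advertisements and information about the study, collecting informed consents, six weeks of intervention (including pre- and post-intervention tests". It adds that "we will be able to perform intervention and data collection in each participating institute twice, six months apart".
- **Recall window.** The JCAMA section states: "All the items are rated on a six-point scale based on the total number of occurrences over the past month". It does not limit the count to time spent inside the institution.

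On analysis, the Data Analysis section says: "The Test 1 and 2 scores within the groups will be compared using the Wilcoxon signed-rank test". Groups are compared by Mann–Whitney tests, with GEE to allow for clustering by institution. BSI is the primary outcome, and aggressive antisocial behaviour is among the secondary outcomes.

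**The concern.** JCAMA counts such events as fights, assaults, conflicts, self-injury and suicide attempts. The Introduction says adolescents are placed because of drug abuse, crime or other destructive behaviour, and that the homes may detain and restrain them. A month that straddles placement and a month wholly inside are therefore counts from two different settings.

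Two comparisons are exposed. The within-group signed-rank test attributes the whole change between the tests to the period of the intervention, although for recent arrivals the setting changed as well. The between-group comparison is exposed because adolescents choose their own group. If newcomers and longer-stay residents choose yoga at different rates, the two groups' baselines cover different mixtures of settings. Mann–Whitney cannot adjust for that, and the stated purpose of GEE is clustering only. Lower aggression and antisocial behaviour are named hypotheses in the Abstract.

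**Working it through.** The article gives no figure for this point, so there is none to reproduce. The check asks how much of the Test 1 window can fall before placement, and for how many participants.

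**1. Share of the window for one participant.** Take a month as 30 days, and let t be the days from placement to Test 1. The pre-placement share is max(0, 1 − t/30).

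| t (days) | Share before placement |
|---|---|
| 0 | 100% |
| 7 | 23/30 = 77% |
| 14 | 16/30 = 53% |
| 21 | 9/30 = 30% |
| 30 or more | 0% |

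More than half of the window is pre-placement only if t is below 15 days.

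**2. Test 2.** At 42 days after the start, the window runs from about day 42 − 30 = 12 to day 42. Everyone tested at Test 1 is already placed, so the pre-placement share is 0%.

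**3. Length of the recruitment phase (assumed).** Three months is about 13 weeks. Subtracting six weeks of intervention leaves 7. Subtracting two more for the interview contacts in the Data Analysis section leaves 5. So 5 to 7 weeks (35 to 49 days) is used.

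**4. Average share over participants.** If t is spread evenly over 0 to T days, with T at least 30, the mean share is 15/T and the proportion with any pre-placement days is 30/T.

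| Who enters | T (days) | Mean share | Any pre-placement days |
|---|---|---|---|
| Only arrivals in a 5-week phase | 35 | 43% | 86% |
| Only arrivals in a 7-week phase | 49 | 31% | 61% |
| Cross-section of residents, 164-day stay (Introduction) | 164 | 9% | 18% |
| Cross-section of residents, 8-month stay (Participants) | 243 | 6% | 12% |

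**5. Which row is nearer?** The Introduction gives about 206,000 care days at 164 days each: 206,000/164 ≈ 1,256 placements a year. Over 23 homes that is about 55 per home per year, or about 5 in five weeks and 7 in seven weeks, if placements are evenly spread. The plan has 3 institutions × 2 = 6 waves for about 120 participants, so 120/6 = 20 per wave. Arrivals within the recruitment phase would not fill a wave. The rest would have to be adolescents already resident, which gives a mixture of newcomers and longer-stay residents.

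**The case against.** The strongest objection is that an offer on arrival is not a test on arrival. The Participants section ties both tests to a wave, so many participants will have lived in the institution for weeks or months by Test 1. That stands. A reader might infer from the inclusion criterion that Test 1 chiefly measures life before placement for participants in general. The article does not support this: it would require most participants to be tested within about 15 days of placement, and steps 4 and 5 make that unlikely.

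A reader might also infer that JCAMA must fall in both groups. This is not supported either. The article gives no JCAMA level before or after placement. The Introduction reports 1,152 uses of physical restraint in 2019, so life inside is not shown to be low in aggression, and counts could move either way. Nor does it say that every adolescent comes straight from the community. A bias in JCAMA points cannot be obtained by applying the window share to assumed scores: items are banded frequencies, and a mixed window mixes event counts, not banded scores.

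Further, a change of setting occurs in both groups, so the between-group contrast suffers only if time since placement differs by group. The Discussion already concedes the lack of randomisation. This is correct, but a general concession does not control a specific source of imbalance that can be measured.

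Finally, visit timing and covariates may be detailed in a fuller document. However, the enrolment point, the recall window and the wave schedule are all stated here, and together they leave the baseline undefined for recent arrivals.

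**Conclusion.** The point holds in a limited form. For participants tested within a month of placement, the two JCAMA windows cover different settings, and their within-group change cannot be assigned to yoga. The between-group contrast is biased if time since placement is related to the choice of group, which self-selection permits but the article does not show.

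The average pre-placement share of the Test 1 window is about 6% to 43%. The upper part of that range (31% to 43%) applies only if enrolment is confined to arrivals in a 5 to 7 week recruitment phase. These figures assume a 30-day month, evenly spread arrivals and waves run as described; Figures 1 and 2 could not be seen. The wave schedule lowers the average share, but by mixing newcomers with longer-stay residents it creates the condition under which the groups can differ.

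The point concerns a secondary outcome tied to a named hypothesis. It does not carry over to BSI, for which no one-month window is stated.

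**What to change.** 1. State how Test 1 relates to placement, so that the inclusion criterion, the Procedure section and the wave schedule agree. Record the placement date, or days from placement to Test 1, in the coded data. This must be done before the code keys are destroyed, which the Procedure section schedules for the end of data assessment.
2. Include days from placement to Test 1 as a covariate in the between-group GEE model for JCAMA. If both tests enter as outcomes, include its interaction with time, since a main effect alone would not adjust the change. Allow the effect to level off at 30 days, where the pre-placement share reaches zero.
3. Repeat the JCAMA analysis in participants with at least one month in the institution at Test 1.
4. Report the within-group JCAMA change as descriptive, not as an effect of yoga.

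The cost is one date that the institution should already hold, one covariate (with its time interaction where needed) and one extra analysis. The sensitivity analysis will be smaller: it loses about 12% to 18% of participants if they resemble a cross-section of residents, but 61% to 86% if only arrivals in the recruitment phase enter, in which case it would be weak and the covariate would carry the weight. Delaying Test 1 for everyone is not needed and could cost recruits in a study that already expects attrition of up to 50%. The same covariate for BSI is optional.
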